### Allocation randomization and hiding

Patients will be randomly allocated into two groups: Control Group (CG) and Experimental Group (EG). Their allocation will be guaranteed through the “Research Randomizer” website so that all patients have an equal chance of becoming part of one group or another.

#### Blinding

The study will have the participation and involvement of two researchers. Researcher 1 (R1) will be responsible for the recruitment and initial selection of individuals that will compose the sample, as well as for guaranteeing their participation by signing the Free and Informed Consent Form (FICF), performing the randomization and allocation of patients and application of headphones in both groups. The second researcher will be responsible for applying the data collection instruments during the intervention and at the end of the painful procedure. Thus, the second researcher, service health professionals and patients will not know to which groups patients will be allocated.

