**Methods:**

This is a randomized controlled clinical trial, with two arms and a single-blind design to be carried out with 68 patients equally allocated into control and experimental groups. The intervention will be applied with the use of headphones without any musical transmission in the control group or with the patient’s musical preference in the experimental group with sound intensity of 60 dB. These patients will be evaluated in three moments: immediately before, during and 15 min after the painful procedure. The primary outcome includes reduction of pain intensity verified by the Visual Analogue Scale and the secondary outcome corresponds to improvement of vital signs and vocal and facial pain expressions.

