#### Interventions

The Control Group (CG) will be composed of 34 patients allocated in a simple random way with clinical indication of performing cardiac catheterization. These patients will receive the standard care already adopted by the service, in addition to the application of headphones without any musical transmission for the removal of the arterial sheath via the femoral route in a timely manner and will remain with the headphones for 15 min after the end of the painful procedure.

The Experimental Group (EG), in turn, will be composed of 34 patients allocated in this group in a simple random way, who will receive the same care as the previously mentioned group, in addition to the application of headphones which will transmit the patient's musical preference during the performance of the painful procedure up to 15 min after its completion. The headphones will be used in a complementary way and not as a substitute for the care already adopted by the service.

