### Screening

Immediately before carrying out the procedure, the first researcher will recruit the possible subjects and explain the main study objective, the possible risks and benefits involved in the study and emphasize that he/she may withdraw from participating in the research at any stage of it.

If there is affirmative answer, this first researcher will apply the inclusion and exclusion criteria to select the individuals who will compose the sample. Then, they will be asked to read and sign the Free and Informed Consent Form (FICF) to guarantee their participation in the study.

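### One unblinded researcher screens, consents, randomises and allocates with no stated concealment, replacements inherit a known arm, and 'simple' allocation does not fit a fixed 34/34 split

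*Protocol article*

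**What the plan says.** **Roles.** Under Blinding, R1 "will be responsible for the recruitment and initial selection of individuals that will compose the sample", obtains signed consent, and is also responsible for "performing the randomization and allocation of patients and application of headphones in both groups". Under Screening, "this first researcher will apply the inclusion and exclusion criteria to select the individuals who will compose the sample". The exclusions listed under Eligibility and recruitment criteria include not liking music, chronic pain, and neurological or cognitive problems that impair use of the pain scale.

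**Blinding.** The second researcher, the service staff and the patients are said not to know the group. R1 is not in that list.

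**Concealment.** The section Allocation randomization and hiding says: "Their allocation will be guaranteed through the “Research Randomizer” website so that all patients have an equal chance of becoming part of one group or" the other. It names no list holder, envelope or third-party release.

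**Order.** Under Follow-up, and in Table 1, eligibility and consent come before allocation.

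**Type and totals.** Under Interventions, the control group "will be composed of 34 patients allocated in a simple random way with clinical indication of performing cardiac catheterization", and the experimental group "will be composed of 34 patients allocated in this group in a simple random way". The abstract's Methods has "68 patients equally allocated into control and experimental groups".

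**Replacement.** Under Data management, a patient who withdraws is replaced by the next eligible patient, who enters the arm that the withdrawn patient left, until the planned number is reached.

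**The concern.** Randomisation prevents selection bias only if the person who decides on entry can neither know nor influence the next assignment. Here that person also carries out the randomisation, and some of the entry decisions are matters of judgement. If R1 knows or can change the next arm, a patient who seems likely to respond well to music could be taken in, passed over or re-drawn, with no trace in the data.

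The pain score in the primary outcome is self-reported, and there are only 68 patients. Blinding the second researcher protects the measurement but not the composition of the arms. Adjustment for measured baseline variables could remove part of such a bias, but not the part carried by unrecorded impressions at screening.

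The description of the randomisation adds to the problem. If allocation is simple, the totals are not fixed. If the totals are fixed, allocation is restricted, and the form of restriction determines how much someone counting past assignments can predict.

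**Working it through.** **1. Who can foresee or steer an assignment?** The document does not say whether the website is used once to make a list or separately for each patient. Both cases are open.

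| Use of the website | Protection from consent before allocation | What stays open to R1 |
|---|---|---|
| List made in advance, visible to R1 | None: R1 can know the next arm while screening | Foresight: approach, exclude or delay according to the arm |
| Draw made per patient, after consent | R1 cannot foresee an ordinary draw | Steering: repeat the draw or withhold it |
| Replacement after a withdrawal | None: the arm is set by the withdrawal | The arm can be known before the patient is approached |

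The first two rows are conditional on facts not given. The third follows from the stated rule, because R1 performs the allocation and so can know which arm the withdrawn patient left.

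**2. Does simple randomisation give 34/34?** Inputs: 68 patients and 34 per arm (Sample size; Interventions). Assumption: 'simple' means independent 1:1 draws.

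- P(exactly 34/34) = C(68,34) / 2^68 = 0.0964, or 9.6%.
- P(smaller arm between 30 and 34) = sum of C(68,x) / 2^68 for x = 30 to 38 = 0.725. So P(39/29 or more uneven) = 1 − 0.725 = 0.275.

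The fixed split therefore needs a cap or a restricted list.

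**3. How much would fixed totals alone reveal?** This assumes someone who sees past assignments but not the list. Let n = 34 per arm.

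- *Random ordering of 34 + 34 labels.* The expected length of the final run, which is certain once the other arm is full, is 2n/(n + 1) = 68/35 = 1.94. Simulation of 100,000 lists gives 1.94.
- *Same list, always guessing the less-filled arm.* Expected correct guesses = n + ½ × (2^68 / C(68,34) − 1) = 34 + ½ × (1/0.0964 − 1) = 34 + ½ × 9.37 = 38.7 of 68, or 56.9%. Simulation of 20,000 lists gives 38.7. Pure guessing gives 34, or 50%.
- *Coin toss until one arm reaches 34, the rest forced.* Expected forced assignments = 68 × 0.0964 = 6.6. Simulation of 100,000 runs gives 6.6, with median 6 and 5th to 95th percentile 1 to 15.

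So the fixed totals alone make about 2 to 7 assignments certain on average, depending on a scheme that the article does not name. The larger exposure is the combined role in step 1.

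**The case against.** The strongest reply is that this is a condensed article. Who holds the list, and whether envelopes are used, are details commonly left to the full protocol, and the word hiding in the heading suggests that concealment was considered. The absence of envelopes would be no finding on its own. What remains is what the article does state: enrolment and randomisation belong to one unblinded person. A full protocol that agreed with the Blinding section would keep that arrangement.

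A reader might infer that R1 holds a list and can foresee all 68 assignments. The documents do not support that. Performing the randomisation also fits a draw made per patient after consent, which is the stated order. That would leave steering possible but not foresight. Nothing shows that either has happened.

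A reader might also take the 9.6% and 27.5% as the size of a bias. They are not. They describe independent draws, and a split such as 39/29 arising by chance costs little precision and causes no bias. 'Simple' may be loose wording for an unstratified random ordering of 34 + 34 labels, which does give each patient an equal chance. That would be restricted randomisation, so the wording still needs correcting.

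Finally, any scheme with fixed totals has some forced assignments, including permuted blocks. This is true, and it is why the proposed blocks vary in size and the envelopes stay sealed.

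**Conclusion.** The concern stands in three parts of unequal strength.

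1. **Combined role without stated concealment.** The opportunity for selection bias follows from the role description itself. Whether it takes the form of foresight or steering depends on how the website is used, which is not stated. The resulting bias cannot be quantified from the document.
2. **Replacement rule.** Each replacement's arm is non-random and can be known before the patient is approached. The number affected equals the number of withdrawals replaced, for which no rate is given.
3. **'Simple' against 34/34.** This is a wording conflict. Independent draws give the stated split 9.6% of the time, so some restriction must be meant and should be named. Predictability from the fixed totals alone is modest: about 1.9 certain assignments with a fixed list, or 6.6 with a capped coin toss.

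The plan should be changed. The remedy is cheap, and analysis could repair only part of any bias that arose.

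**What to change.** - **Allocation randomization and hiding, and Blinding:** state that someone who neither recruits nor assesses outcomes generates the list once, in permuted blocks of varying size, and seals it in sequentially numbered, opaque envelopes. R1 opens the next envelope only after eligibility and consent are recorded. R1 may still apply the headphones.
- **Interventions:** delete 'simple' for both groups and describe 34 per arm as the target.
- **Data management:** give any additional patient the next concealed assignment instead of the withdrawn patient's arm. Prepare some envelopes beyond 68 for this.

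The cost is one session to prepare the envelopes, a few changes of wording, and final arm sizes that may differ slightly from 34/34. It assumes that the team can find one person outside recruitment and outcome assessment for that single task. No extra staff are needed on the ward.

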### Trial design

This is a protocol of a Randomized Controlled Clinical Trial (RCT) with two arms and single-blind intervention design, which compares the effects of music therapy to relieve pain in adults and older adults during femoral arterial sheath removal after cardiac catheterization with standard interventions already used by the service for this same procedure.

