#### Questionnaire

At first, the principal researcher will apply a form previously prepared with participants of both groups containing the following sociodemographic data: date of birth, age, sex, color, marital status, schooling, profession, family income and musical preference.

At this time, the initial part of the second previously prepared form will also be applied, containing the following clinical data: comorbidities, reason for performing cardiac catheterization and medications in use. After completing this part, blood pressure, heart and respiratory rate vital signs will be measured, as well as information regarding oxygen saturation, presence or absence of bodily signs and symptoms of pain such as sweating, pallor, vocal or face expression or pain. These data will be recorded in the second previously prepared form and repeated during the intervention and 15 min after the end of the painful procedure.

This second form also contains information regarding the French number of the arterial sheath, the professional responsible for removing it, if there were complications during the painful procedure and what these complications were; if there were complications after the procedure and what these complications were; how long the arterial compression lasted after the intervention; if there was need for analgesia after the procedure and the time to receive the hemodynamic discharge. Finally, the Visual Analog Pain Scale will be applied to identify pain intensity.

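### The Blinding section wrongly says that patients will not know their group; they hear either their own preferred music or silence, and they then rate the VAS themselves

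*Protocol article*

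**What the plan says.** The Blinding section splits the work between two researchers. The first recruits, obtains consent, randomizes, allocates and puts the headphones on in both groups. The second applies the data collection forms during the intervention and at the end of the procedure. The section concludes that "the second researcher, service health professionals and patients will not know to which groups patients will be allocated".

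The Interventions section defines the two conditions. Controls receive standard care plus "application of headphones without any musical transmission for the removal of the arterial sheath via the femoral route". The experimental group receives the same care, with headphones carrying the patient's "musical preference during the performance of the painful procedure up to 15 min after its completion".

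Before this, under Screening, the first researcher is to "explain the main study objective, the possible risks and benefits involved in the study". Under Questionnaire, a form completed in both groups ends with "marital status, schooling, profession, family income and musical preference".

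The Trial design section describes a trial "with two arms and single-blind intervention design" without naming the blinded party. The Methods part of the Abstract uses the same label.

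**The concern.** The document claims a property that its own interventions rule out. Music against silence cannot be hidden from the person wearing the headphones.

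This matters because the pain VAS is the patient's own rating, so the patient is in effect the outcome assessor. Masking whoever holds the form does not mask the rating. Patients who hear their chosen music may expect relief and report less pain. Patients who named their preferred music and then got silence may be disappointed and report more. Either would separate the arms on the VAS without any analgesic effect. A report that repeated the present statement would present a self-rated primary result as patient-blinded and overstate how certain it is.

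The labels add to the problem. Single-blind does not fit a section that lists three unaware parties. A reader who has to guess which one is meant may well choose the patient, the one party for whom the design excludes it.

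**Working it through.** The blinding claim contains no figure to reproduce, so the first step sets the sections of the protocol article side by side.

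**1. Can the patient perceive the allocation?**
- Eligibility and recruitment criteria: people with hearing impairment are excluded, as are people who do not like music. Every participant can therefore hear whether music is playing.
- Questionnaire: musical preference is recorded in both groups, so controls have also been asked what they like.
- Interventions: the experimental group hears that preferred music; controls have "application of headphones without any musical transmission for the removal of the arterial sheath".
- Conclusion: the patient perceives the assigned condition directly.

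**2. Is the patient aware when the primary outcome is recorded?**
- Background: the VAS is described as a self-assessment by the patient.
- Primary outcome: VAS pain intensity is named first.
- Follow-up: the VAS is applied after 15 minutes of compression, once the headphones are off. The patient has by then been through the whole assigned condition.
- Conclusion: yes.

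**3. Does the same reasoning reach the observers?**
- Both arms wear headphones, so a person looking on sees the same thing in each arm.
- Only the first researcher allocates and applies the headphones; a different person collects the data.
- Follow-up already places headphone removal before the last part of the form and the VAS.
- Conclusion: no. Observer masking could fail through sound leakage or a patient's remark, but no section shows that it does.

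**4. Which outcomes are affected?**
- Affected: the VAS and, among the secondary outcomes, signs voiced by the patient such as a verbal report of pain.
- Still able to benefit from a masked observer: blood pressure, heart rate, respiratory rate and oxygen saturation, and observed signs such as pallor and sweating. The Primary outcome section lists the four vital signs beside the VAS; the Abstract makes vital signs secondary.

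**5. What could reporting bias do? (illustration only)**
- Input from the Sample size section: 34 per group, significance level 5%.
- Assumptions, none of them in the document: no true effect; a pure reporting shift of b standard deviations between arms; a two-sided two-sample t-test.
- Degrees of freedom: 34 + 34 − 2 = 66. Critical value: 1.997.
- Noncentrality: δ = b × √(34/2) = b × 4.123.
- Rejection probability: P(|T| > 1.997), where T is noncentral t with 66 degrees of freedom and noncentrality δ.

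| Assumed shift b (SD) | δ | Probability of p < 0.05 |
|---|---|---|
| 0 | 0 | 5% (nominal) |
| 0.1 | 0.412 | 6.9% |
| 0.2 | 0.825 | 12.8% |
| 0.3 | 1.237 | 23.0% |
| 0.4 | 1.649 | 36.9% |

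All of these shifts lie below the effect of 0.50 used in the Sample size section. The table shows sensitivity to bias. It does not estimate the bias in this trial.

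**The case against.** **The statement may mean only that patients are not told their group.** That reading is possible but weak. Everyone is asked for a musical preference, and the headphones then reveal the condition without anyone saying it.

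**How much patients expect is unknown.** Screening says that the main objective is explained but not how much of the comparison is disclosed, and the consent text is not available. This stands: the strength of any expectation cannot be established here. The contradiction between Interventions and Blinding does not depend on it.

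**Patient blinding is impossible with audible music, so no design is at fault.** This also stands. Comparing music with silent headphones is legitimate. The fault is the statement that patients are unaware.

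**A reader might infer that the stated blinding fails altogether, and that nothing keeps the second researcher from learning the group.** The document does not support this. Headphones in both arms and the split of tasks between the two researchers are masking steps. Finer operational detail, such as who starts and stops the sound, is what an article commonly leaves to the full protocol, so its absence is no defect.

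**A reader might also infer that the whole primary outcome is self-reported.** It is not as the Primary outcome section words it, because vital signs are listed there too.

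**The bias figures have no source in the document.** Correct. They also assume a t-test, which the statistical analysis section does not name, and they should carry no weight in judging how serious the point is.

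**Conclusion.** The point holds for patients and for what patients report. The article affirms patient blinding that its own interventions exclude, and the VAS rating is made by a person aware of the condition received. This is a wrong statement, not a detail left out by a condensed article, and no fuller document could make it right.

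The point does not extend to the second researcher or the service staff. Their masking is plausible, not disproved, and still useful for the vital signs and observed signs.

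The size of any bias on the VAS is unknown. The range of about 7% to 37% against a nominal 5% rests wholly on assumed shifts of 0.1 to 0.4 SD with no true effect, and is illustrative only. The consequence that can be stated firmly is one of interpretation: a VAS difference would be a comparison of music with silent headphones in aware patients, open to reporting bias. The statement should be corrected; the design, sample and schedule need not change on this account.

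**What to change.** 1. In Blinding, state that patients are not blinded. Name the second researcher as masked, and the service staff too if their masking is maintained.
2. In the Abstract and Trial design, replace the single-blind label with assessor-blind, and say who the masked assessor is.
3. State that conclusions on the VAS concern music versus silent headphones in patients who know which they received, and that reporting bias is possible. Note that observer masking can still protect the vital signs and observed signs.
4. As inexpensive support for observer masking, ask patients not to tell the second researcher what they hear.

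The cost is a few sentences and one instruction to patients. The downside is a weaker blinding claim.

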#### Data management

First, two researchers (R1 and R2) will be trained to perform data collection, in accordance with the study protocol. The information will be collected in the patient's admission/recovery room and stored in database previously built in Microsoft Excel. Subsequently, data will be exported to the Statistical Package for Social Science Version 18.0 software (SPSS Version 20.0) in order to perform descriptive and inferential analyses. Therefore, data will be presented through tables, charts and figures.

It is worth mentioning that losses and dropouts will be carefully recorded in order to ensure study reliability. Therefore, whoever withdraws from participating in the research will be replaced by the next participant who meets the inclusion and exclusion criteria, being included in the group referring to the withdrawal until reaching the previously calculated sample number. All information will be stored in a safe place by the responsible researcher for a period of five years and will only be presented in scientific publications, preserving the anonymity of participants.

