### Sample size

The sample size calculation was performed using the G Power software, version 3.1.9.2, with Cohen effect of 0.50, test power of 0.80 and significance level of 5%, establishing N of 34 patients per group, experimental and control, totaling 68 patients.

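### Placing each replacement patient in the withdrawn patient's group makes that assignment non-random and known to the recruiter before enrolment

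*Protocol article*

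**What the plan says.** All references are to the protocol article.

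- **Data management.** On withdrawal, "whoever withdraws from participating in the research will be replaced by the next participant who meets the inclusion and exclusion criteria", the newcomer "being included in the group referring to the withdrawal until reaching the previously calculated sample number". The same paragraph says that "losses and dropouts will be carefully recorded in order to ensure study reliability".
- **Allocation randomization and hiding.** A randomisation website is used "so that all patients have an equal chance of becoming part of one group or another".
- **Interventions.** Each group of 34 is described as formed by simple random allocation.
- **Screening and Blinding.** Researcher 1 recruits, applies the eligibility criteria and obtains consent. Researcher 1 is also responsible for "performing the randomization and allocation of patients and application of headphones in both groups".
- **Sample size.** The target that ends replacement is given as "establishing N of 34 patients per group, experimental and control, totaling 68 patients".
- **Follow-up, Table 1.** The VAS is marked only at F1, 15 minutes after sheath removal.

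**The concern.** Randomisation protects the comparison only for patients whose arm is drawn by chance and is unknown when the decision to enrol is made. The replacement rule breaks both conditions for every replacement. Some exclusion criteria also need judgement: not liking music, chronic pain, and cognitive problems that compromise use of the scale. A recruiter who knows that the next patient will get music, or silent headphones, can let that knowledge affect who is judged eligible or how the study is presented. This need not be deliberate.

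A second issue follows from the stopping point. If replacement continues until each arm again holds 34, the natural reading of the 68 is those who did not withdraw. That invites a comparison of stayers instead of a comparison of everyone randomised.

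**Working it through.** **Step 1: set the statements side by side.**

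| Patient | Arm decided by | Chance of music arm | Known to Researcher 1 before consent? |
|---|---|---|---|
| Ordinary recruit | Random list | 1/2 (equal chance stated) | Not if the list is concealed |
| Replacement | Arm of the withdrawn patient | 0 or 1 | Yes |

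The equal-chance and simple-random statements cannot hold for the second row. This is a conflict between rules that the article states, not a missing detail. An analysis plan could not repair it, because it cannot randomise patients who were assigned by rule.

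**Step 2: trace who knows what.** Screening, consent, allocation and headphone application all belong to Researcher 1. That researcher applied the withdrawn patient's headphones and so knows the vacated arm. The next eligible patient must go there, so the arm is known before that patient is approached.

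**Step 3: how many patients are affected.** The documents give no withdrawal rate. Assume that each enrolled patient, original or replacement, withdraws with probability w, and that replacement continues until 34 per arm remain.

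- Enrolled per arm: 34/(1 − w).
- Replacements enrolled per arm: 34/(1 − w) − 34 = 34w/(1 − w).
- Replacements who stay, per arm: 34w/(1 − w) × (1 − w) = 34w.
- Replacements among the 68 counted: 68w.

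| Assumed w | Replacements enrolled per arm | Non-randomly assigned among 68 |
|---|---|---|
| 5% | 1.8 | 3.4 |
| 10% | 3.8 | 6.8 |
| 15% | 6.0 | 10.2 |
| 20% | 8.5 | 13.6 |

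These are counts of patients affected, not estimates of bias. The bias depends on how far selection into a known arm shifts the patient mix, which nothing in the documents allows one to estimate.

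**Step 4: what random allocation with a buffer would need.** The list per arm is 34/(1 − w), rounded up: 36, 38, 40 or 43 for w of 5%, 10%, 15% or 20%.

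The figure of 34 enters only as the point where replacement stops. It does not reproduce for two independent groups at the stated effect size, power and significance level (64 per group two-sided, 51 one-sided, by t test). That is a separate matter on which this point does not depend.

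**The case against.** **Few patients may be involved.** The procedure is short, assessment ends 15 minutes after sheath removal, and the headphones start only at removal. Withdrawals may be rare, and silent headphones cannot cause those that occur earlier. This stands and limits the likely impact. It does not make the rule sound, since the contradiction and the loss of concealment begin with the first replacement.

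**A reader might infer a calculable bias from the rule.** For example, suppose that the true standardised difference is 0.50 and that the 10% of controls with the highest pain withdraw. The mean of a normal variable with its top 10% removed falls by φ(1.2816)/0.90 = 0.1755/0.90 = 0.195 SD, so the apparent difference is 0.50 − 0.195 = 0.305. But that is the effect of informative dropout. Replacements who stay come from the same truncated distribution, so the expected control mean is the same with or without them. Simulation gave 0.305 with replacement and 0.304 without, with power of 0.27 and 0.26. Such figures therefore do not measure the harm of this rule, and the withdrawal pattern behind them is extreme and has no support in the documents. If withdrawal is unrelated to pain, there is no dropout bias.

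**A reader might infer that withdrawn patients are dropped from the analysis.** The article does not say so. It says that losses are recorded and names no analysis population, which an unseen full protocol or analysis plan may do. The rule invites a completers-only count but does not prescribe one.

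**A reader might infer that the damage is beyond repair at analysis.** For dropout this is too strong, because recorded losses can be reported by arm and examined in sensitivity analyses.

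**Conclusion.** The concern holds as a flaw in allocation. The replacement rule contradicts the article's own statements on randomisation and removes concealment for every replacement, because one researcher recruits, applies the criteria, obtains consent and allocates. This follows from the text and needs no assumption about the withdrawal rate.

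The number of patients affected does rest on an assumption: about 68w of the 68, if a share w withdraws. The size and direction of any resulting bias cannot be derived from the documents, and no figure should be attached to them. That the final analysis would cover completers only is a reasonable worry, not a stated plan.

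The rule should be corrected before recruitment relies on it. The change is simple and protects the random allocation on which the comparison rests.

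**What to change.** 1. Delete same-group replacement. Give every newly enrolled patient the next concealed random allocation, whatever has happened to earlier patients.
2. If a buffer for losses is wanted, lengthen the random list in advance. With 34 as the target, an assumed 10% loss means 38 per arm.
3. Keep all randomised patients in their assigned group, use data collected up to withdrawal where consent allows, and report withdrawals by arm.
4. Add a sensitivity analysis for missing VAS scores. With the VAS scheduled only at F1, anyone who withdraws earlier lacks the primary pain score. Steps 1 to 3 restore random allocation and concealment but do not by themselves remove dropout bias.

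Cost: mainly a change of wording, plus the sensitivity analysis and a few extra enrolments if a buffer is used. The arms may end slightly unequal, or a few patients short of 34 evaluable.
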